#### Secondary back pain outcome analyses

For pain medication use, we will examine the overall use during the previous week at week 12. First, a chi-square test will be used to compare medication use at week 12 between groups. Next, logistic regression with terms for treatment group and adjusting for potential confounders, including baseline pain medication use, will be used to compare medication usage rates. Use of medication subtypes, including nonsteroidal anti-inflammatory drugs, acetaminophen, and opioids, will be similarly compared. We will report odds ratios with corresponding 95 % confidence intervals and *p* values. Physical and mental health summary scores will be calculated from SF-12 data using population normative data and means compared between groups as for the primary outcomes above. We will also compare the proportion of participants in each group achieving ≥30 % and ≥50 % improvements from baseline for the co-primary outcomes, often considered to correspond to minimal and moderate clinically meaningful change, respectively.

#### Psychological and exploratory analyses

Our hypothesis is that yoga will be superior compared to education for reducing PTSS in the subset of participants with comorbid PTSS (baseline PCL-C ≥30). We will first compare PCL-C scores between groups for the subset of participants who qualify as having PTSS at baseline using methods similar to those described above for primary outcome analyses. We will also examine the whole study sample and the subset of participants with lower baseline PCL-C scores. We stratify for this variable during randomization and thus anticipate similar numbers and baseline characteristics between the two study groups. We will also explore whether a change in PTSS is an effect modifier for our primary outcomes of pain and function. We will similarly compare yoga to education for the subgroup of participants with moderate or greater depressive symptoms (PHQ-9 ≥10) [97] and those with less depressive symptoms. Exploratory subset analyses will also be conducted for Veterans scoring moderate or higher on anxiety symptoms (GAD-7 ≥10) and sleep difficulties (PSQI >5). Similarly, an exploratory subset analysis will be conducted for participants with post-concussive symptoms, defined as scoring ≥20 on the NSI [98].

Since back pain in older Veterans may be different structurally compared to younger Veterans, we will also complete exploratory subset analyses of Veterans ≤45 and >45 years old to assess if age confounds the response to yoga.

To analyze intermediate-term outcomes, we will examine changes from baseline to week 6 using methodology similar to the primary 12-week analyses. Additional subgroup longitudinal analyses can be done using only data from those participants who were 12-week completers. We will also compare the change in pain medication usage over time using a generalized-estimating equation approach or nonlinear mixed effects model to account for the repeated measures of a dichotomous outcome. This approach will parallel the longitudinal analyses for continuous outcomes described above.

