## Background

### Low back pain in Veterans

Musculoskeletal pain conditions are the most commonly diagnosed medical problems among the more than two million Veterans from Operations Enduring Freedom, Iraqi Freedom, and New Dawn (OEF/OIF/OND), far surpassing other medical and mental health disorders [1–3]. In a study of 91,000 Veterans receiving care from the Veterans Health Administration (VHA), 43 % reported having any pain, and 63 % of these reported moderate to severe pain [4]. Eighty percent of VHA visits include pain-related complaints [5]. Overreliance on opioids is common and can lead to adverse effects ranging from sedation to dependence, addiction, and death due to overdose [6, 7]. Among pain conditions, chronic low back pain (cLBP) is the most frequent [4] and causes substantial suffering, decreased functional capacity [8], and lower quality of life [9, 10]. The direct costs of chronic pain in the U.S. are estimated to be $100 billion or greater annually [3]. Among Veterans, back pain is a leading cause of disability [11, 12].

Psychological distress, back pain, and disability are strongly correlated. Symptoms of post-traumatic stress [13], depression [6], and traumatic brain injury [1] are highly prevalent in Veterans with cLBP [14]. Among Veterans receiving care from VHA Polytrauma Network sites, 42 % had the triad of chronic pain, post-traumatic stress symptoms (PTSS), and persistent post-concussive symptoms (traumatic brain injury) [7, 15]. Low pain self-efficacy and maladaptive pain coping behaviors (e.g., catastrophizing [16], fear avoidance [17], and substance abuse [18]) compound back pain recovery. Moreover, stigma and other barriers often prevent Veterans from seeking mental health care (e.g., cognitive therapy for PTSS), leading to additional barriers to back pain recovery [19, 20].

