### Sample size

We assume a two-sided α = 0.05. This is justifiable because, although there are two primary outcomes, they are not independent. We use 2.5 as the standard deviation for the mean pain change score between baseline and 12 weeks, which is what was found in previous yoga-cLBP studies [37]. We also assume a 20 % dropout rate based on previous studies [37]. Thus, a sample size of 120 participants randomized to yoga vs. education provides 97 % power to demonstrate a minimal clinically significant difference in pain score of 2.0 [74]. For the RMDQ change score, if we assume a standard deviation of 5.0 [35, 37] and a minimal clinically significant difference of 3.0 [75], we have 82 % power to show a statistically significant difference between the two groups. Finally, if we assume that 50 % of the study participants with cLBP have a baseline PTSD CheckList – Civilian Version (PCL-C) score ≥30 and a standard deviation for the PCL-C change score of 12 [76, 77], there is 80 % power to demonstrate a minimal clinically meaningful difference in PCL-C of 10 points.

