### Randomization

The baseline survey is typically completed within 45 days after eligibility screening. If the period since screening exceeds 45 days, eligibility is re-assessed and verified prior to the baseline survey. After completion of the baseline survey, the participant is randomized in a 1:1 ratio to yoga or education using StudyTRAX™ (Macon, GA), a HIPAA-compliant study management software platform. Permuted block randomization with varying block sizes of two or four is used. Stratification is done on three dichotomous variables to assure similar distribution between the two groups:Age (≤45, >45 years). Back pain in older Veterans may be structurally different. Furthermore, age may be a confounding variable to the response to yoga.PCL-C score (<30, ≥30). These cut-offs will help assure equivalent numbers of Veterans with PTSS in both treatment arms in order to compare the effectiveness of the interventions for reducing comorbid PTSS. PTSS may also be an effect modifier for yoga and cLBP.Partnered (yes/no). A partnered Veteran is defined as one who reports having a cohabitating or long-term committed partner/spouse. This helps assure adequate numbers of partnered Veterans in the yoga group available for qualitative interviews.

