### Data collection

Outcome data are collected at baseline, 6 weeks, 12 weeks, and 24 weeks. Participants in both treatment arms complete paper surveys in person and receive cash honoraria after the completion of each survey. We give $25 at baseline, 6 weeks, and 12 weeks. At the final follow-up at 24 weeks, participants receive $50 after completion of their survey. Paper surveys are double-entered into StudyTRAX™ by research staff who have no knowledge of or access to identifiable participant information or treatment assignment. The two data entries are compared and reconciled.

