#### Outcome measures

Table 3 shows the data collection schedule. Our measures include core patient-oriented outcomes for the cLBP trials, including those recommended by the Report of the NIH Task Force on Research Standards for Chronic Low Back Pain [73]. Change in pain intensity and back-related function are the two co-primary outcomes at 12 weeks [63, 71]. Secondary back pain outcomes include pain medicine use in the previous week, including medication class and dosage [81]; health-related quality of life (SF-12) [82]; pain interference [83]; overall improvement (7-point Likert scale, 0 = extremely worsened to 6 = extremely improved); and patient satisfaction with cLBP treatment (5-point Likert scale, 1 = very satisfied to 5 = very dissatisfied) [84]. Psychological secondary outcomes include post-traumatic stress symptoms (PCL-C) [85] and depression symptoms measured using the 9-item Patient Health Questionnaire (PHQ-9) [86]. The Pittsburgh Sleep Quality Index (PSQI) is also administered [87]. Exploratory neuropsychological outcomes include post-concussive symptoms measured using the Neurobehavioral Symptom Inventory (NSI) [88], 7-item Generalized Anxiety Disorder questionnaire (GAD-7) [89], Coping Strategies Questionnaire (CSQ) [90], and Pain Self-Efficacy Questionnaire (PSEQ) [91]. Exploratory social outcomes include marital/family functioning measured using the Dyadic Adjustment Scale (DAS) [92], employment status (Work Productivity and Activity Impairment questionnaire) [93], and housing status. NIH PROMIS® (Patient Reported Outcomes Measurement Information System) tools [94] for outcomes of interest, such as pain, function, depression, anxiety, and sleep, are used to assess how well they correlate with the DVPRS, RMDQ, PHQ-9, GAD-7, and PSQI. At baseline, we also gather standard sociodemographic information and possible covariates, including race, ethnicity, income, education, military service history, medical comorbidities, back pain history, expectation of helpfulness for the different interventions [95], and preference of treatment assignment.

**Table 3 Tab3:** Schedule of assessments

Measures	Enrollment	Baseline	6 weeks	12 weeks	24 weeks
Screening and enrollment					
Eligibility screening	✓				
Informed consent	✓				
Baseline information					
Sociodemographics*		✓			
Expectations and preference		✓			
Back pain history and comorbidities		✓			
Primary outcomes					
Low back pain intensity (DVPRS)		✓	✓	✓	✓
Back-related function (RMDQ)		✓	✓	✓	✓

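### Change in PTSS is measured after randomization and expected to respond to yoga, so treating it as an effect modifier for pain and function mixes mediation or shared response with modification

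*Protocol article*

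**What the plan says.** The analysis in question is one sentence in the protocol article, under Psychological and exploratory analyses: "We will also explore whether a change in PTSS is an effect modifier for our primary outcomes of pain and function". The variable named is the change, not the baseline level. The sentence gives no model and no time point for the change.

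Other parts of the article show what kind of variable this is:

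- **It is an outcome.** Outcome measures and Table 3 list PCL-C among the secondary outcomes. Data collection states: "Outcome data are collected at baseline, 6 weeks, 12 weeks, and 24 weeks". Any change score therefore uses post-randomization values.
- **Treatment is expected to move it.** The same analysis section states: "Our hypothesis is that yoga will be superior compared to education for reducing PTSS in the subset of participants with comorbid PTSS".
- **It is expected to track pain and function.** The Background states: "Psychological distress, back pain, and disability are strongly correlated". No coefficient is given.
- **A baseline version exists.** Randomization stratifies on PCL-C (<30, ≥30) and remarks: "PTSS may also be an effect modifier for yoga and cLBP". There the variable is the pre-randomization one.

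**The concern.** To ask whether a treatment effect on pain differs by some characteristic, one compares the arms within levels of that characteristic. Randomization makes the comparison fair only if the characteristic is fixed before treatment. Change in PCL-C is not. A Veteran whose PCL-C falls by 10 points with yoga and one whose PCL-C falls by 10 points with a book reached that change by different routes, and they may differ in whatever else drives pain. If yoga moves PCL-C and PCL-C change tracks pain change, the difference between arms at a given PCL-C change is no longer the randomized effect. It omits the part that runs through, or alongside, PTSS.

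At stake is how an exploratory result on the two co-primary outcomes is read. A reader told that PTSS change does or does not modify yoga's effect would be given an answer to a question that this analysis cannot address.

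**Working it through.** **Inputs from Sample size.** Two-sided α 0.05; 120 randomized 1:1; 20 % dropout, so 120 × 0.8 / 2 = 48 evaluable per arm. Pain change: SD 2.5, difference 2.0. RMDQ change: SD 5.0, difference 3.0. PCL-C change: SD 12, difference 10, in the assumed 50 % with baseline PCL-C ≥30, so 24 per arm.

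**The plan's own figures reproduce.** The challenged sentence states no number. The related power figures are:

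| Outcome | Per arm | Stated | Normal | t-test |
|---|---|---|---|---|
| Pain | 48 | 97 % | 97.5 % | 97.3 % |
| RMDQ | 48 | 82 % | 83.6 % | 82.9 % |
| PCL-C | 24 | 80 % | 82.3 % | 80.7 % |

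The inputs can therefore be used as planning values.

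**Shift in the pain difference at equal PCL-C change.** Let r be the within-arm correlation of PCL-C change with pain change. The article gives no value, so r = 0.3 to 0.7 is an assumption. With equal slopes in both arms:

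shift = r × (SD pain / SD PCL-C) × (effect on PCL-C)

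- PCL-C ≥30 subset, effect 10: r × (2.5/12) × 10 = 0.63, 1.04, 1.46 for r = 0.3, 0.5, 0.7.
- Full sample, assuming an effect of 10 in one half and 0 in the other, mean 5: r × (2.5/12) × 5 = 0.31, 0.52, 0.73.
- r = 0, or no effect of yoga on PCL-C: shift 0.

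The shift moves the comparison towards education. For RMDQ, at the same r, the formula gives twice as many points, since 5.0/2.5 = 2.

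**Simulation** (one million participants per scenario, PCL-C effect 10, true pain effect −2.0 for everyone, hence no modification). The yoga-minus-education coefficient at equal PCL-C change was −1.38, −0.96 and −0.54 for r = 0.3, 0.5, 0.7. This agrees with −2.0 plus the shift. With participants split at a PCL-C improvement of 10 points (a cut chosen for the check), the estimates were:

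| r | Improved ≥10 | Improved less | Gap |
|---|---|---|---|
| 0.3 | −1.56 | −1.67 | 0.11 |
| 0.5 | −1.27 | −1.44 | 0.17 |
| 0.7 | −0.95 | −1.21 | 0.26 |

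Both strata are attenuated. The treatment × PCL-C-change coefficient was zero throughout, and the small gaps come from cutting a continuous variable.

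**When false modification appears.** Add the further assumption that PCL-C response varies among yoga participants (extra SD 12) and keep the pain effect at −2.0 for everyone. At r = 0.5 the strata give −0.96 and −1.73, and the slope of pain change on PCL-C change is 0.104 under education but 0.052 under yoga. That looks like modification where there is none.

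**Power of the valid alternative.** Modification by baseline PCL-C compares four cells of about 24 evaluable participants. For pain, SE = 2.5 × √(4/24) = 1.02. For 80 % power the interaction must be (1.96 + 0.84) × 1.02 ≈ 2.9 points, which exceeds the 2.0-point minimal difference.

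**The case against.** The strongest reply is that this is a single exploratory sentence, with no model attached, in a condensed article. The authors may have meant mediation and chosen the wrong term, and the analysis plan may set it right. It is true that no estimator is stated, and that comparing arms at a given PCL-C change is the ordinary meaning of effect modification, not a described procedure. But the term is used in its ordinary sense for PTSS itself under Randomization, and here it is attached to a different variable. As written, the analysis needs correcting under either reading.

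Four stronger readings are tempting, and the article does not support them:

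- **That the analysis would report spurious modification.** The shift calculated above is in the arm difference, not in the interaction. With equal slopes the interaction is zero. A marked false signal needs an added assumption, such as varying PCL-C response, on which the article gives no figures.
- **That effects would point the wrong way.** Under the plan's own effects the estimates are attenuated but keep their sign. Reversal needs a pain effect near zero: with none at all and r = 0.5, the strata show 0.75 and 0.56 points in favour of education.
- **That the 0.6 to 1.5 points apply to everyone.** The 10-point PCL-C difference is planned only for the assumed half with PCL-C ≥30.
- **That the question behind the stratification goes unanswered.** The first reason given for stratifying on PCL-C is the comparison of PTSS reduction, and that comparison is planned. Modification is a secondary remark. That no baseline interaction on pain or function is described is not itself a fault, because such a term is commonly left to the analysis plan.

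**Conclusion.** The point holds, at modest weight. The article names a post-randomization outcome, which it expects yoga to change, as an effect modifier for pain and function. That analysis cannot answer a modification question.

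The size depends on an assumed correlation of 0.3 to 0.7, a linear equal-slope model, and the planned PCL-C difference being real. It is about 0.6 to 1.5 points of pain in the PCL-C ≥30 subset. The full-sample figure of about 0.3 to 0.7 also assumes no PCL-C effect in the other half. The two conditions for a shift are ones that the article itself expects: a yoga effect on PTSS, and a link between distress and back pain.

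A reader might infer that the trial's main result is at risk. It is not: the intention-to-treat week-12 contrast and the power figures do not use PCL-C change.

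**What to change.** Replace the sentence with two separate statements:

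1. **Modification.** An exploratory analysis of whether baseline PCL-C (<30 / ≥30 as stratified, or continuous) modifies the baseline-to-week-12 contrast for DVPRS and RMDQ. In the planned longitudinal model this means adding treatment × time × baseline PCL-C with its lower-order terms. Report the difference between subgroup effects with a 95 % confidence interval, and say that power is low, so that a non-significant result is not read as absence of modification.
2. **Mediation, only if change in PTSS is of interest.** A labelled exploratory mediation analysis with week-6 PCL-C as mediator and week-12 pain or function as outcome, adjusted for baseline values of both. State the assumption of no unmeasured confounding between mediator and outcome, which randomization does not secure.

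The cost is a change of wording and a few model terms. Baseline and week-6 PCL-C are already in the assessment schedule, so there is no new data collection and no change to the sample size or the primary analysis. The change should be made before unblinded data are analysed.

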## Methods/design

### Study design

The trial is a single-blinded 24-week RCT and is divided into two phases: an initial 12-week intervention period followed by a 12-week follow-up period (Fig. 1). Prior to beginning the intervention, Veterans are randomized in a 1:1 ratio into (1) a 12-week series of structured weekly hatha yoga classes supplemented by home yoga practice or (2) education using a comprehensive back pain self-management book, *The Back Pain Helpbook*, supplemented by newsletters that highlight key content [68]. Block-stratified randomization is being used to ensure similar numbers of Veterans in both treatment groups who are ≤45 years old, experience PTSS, and have long-term partners (spouse, live-in partner, or in a live-out committed relationship). During the 12-week follow-up period, yoga participants are encouraged to continue home practice. Those in the education group are encouraged to continue following recommendations from the book.

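### Age is treated as a possible confounder and examined by separate analyses at or below and above 45, but the question is effect modification, which those analyses neither test nor estimate

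*Protocol article*

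**What the plan says.** In the protocol article, *Randomization* lists age (45 or less, over 45) as one of three dichotomous stratification variables. The reasons are that back pain may be structurally different in older Veterans and that "age may be a confounding variable to the response to yoga". The next item, PCL-C score, is described there as a possible effect modifier.

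*Psychological and exploratory analyses* returns to the structural argument and plans exploratory subset analyses on each side of 45 "years old to assess if age confounds the response to yoga". It names no comparison between the two age groups.

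The same section covers other subsets:
- PTSS: a superiority hypothesis within PCL-C ≥30, plus the whole sample and the lower-scoring subset.
- Depressive symptoms: both sides of PHQ-9 10.
- Anxiety, sleep and post-concussive symptoms: only the symptomatic subset is named ("Exploratory subset analyses will also be conducted for Veterans scoring moderate or higher on anxiety symptoms").

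*Data analysis* sets α = 0.05 for all analyses. It handles baseline imbalance separately: the arms are compared on baseline variables, including the stratification factors, and variables that differ are adjusted for.

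**The concern.** The stated purpose and the stated method for age do not match.

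- **Purpose.** Age is fixed before randomization and balanced by stratification, so it can distort the yoga-versus-education contrast only through chance imbalance, which the plan already addresses by adjustment. Splitting the sample at 45 does not assess confounding.
- **Method.** The structural rationale asks whether the effect of yoga is larger or smaller in older Veterans. That is a difference between two treatment effects. Analysing each age group alone gives two effects, each with its own p value, and no estimate of how far apart they are.

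The pair of subset results is the only evidence the article plans on this question. A reader who wants an answer has to set one against the other, and at this sample size one significant and one non-significant result is common even when the effects are equal. At stake is an unsupported statement that yoga helps only one age group.

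**Working it through.** **Inputs, all from *Study design* and *Sample size***
- "We assume a two-sided α = 0.05"; "Veterans are randomized in a 1:1 ratio into" the two arms; 120 randomized.
- "We also assume a 20 % dropout rate based on previous studies": 120 × 0.80 = 96 completers, 48 per arm.
- Pain: difference 2.0, SD of change 2.5 ("We use 2.5 as the standard deviation for the mean pain change score between baseline and 12 weeks"), so d = 2.0/2.5 = 0.8.
- RMDQ: difference 3.0, SD of change 5.0, so d = 3.0/5.0 = 0.6.
- PCL-C: difference 10, SD 12, in an assumed 50 % of participants, which gives 24 completers per arm.

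**Step 1. Reproduce the plan's power.** Two-sample comparison of change scores with n per arm: noncentrality = d/√(2/n), two-sided 0.05, noncentral t.
- Pain, n = 48: 0.8/√(2/48) = 3.92, power 97.2 % (stated 97 %).
- RMDQ, n = 48: 0.6/√(2/48) = 2.94, power 82.9 % (stated 82 %).
- PCL-C subset, n = 24: 0.833/√(2/24) = 2.89, power 80.7 % (stated 80 %).

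The method and inputs match the plan.

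**Step 2. Power within an age group.** The article gives no age distribution, so an equal split is an assumption: 24 completers per arm in each group.
- RMDQ: 0.6/√(2/24) = 2.08, power 53.0 %.
- Pain: 0.8/√(2/24) = 2.77, power 77.4 %.

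**Step 3. Chance that exactly one group is significant when the true effect is the same in both.** The groups are disjoint, so the tests are treated as independent: P = p₁(1 − p₂) + p₂(1 − p₁).
- RMDQ, equal split: 2 × 0.530 × 0.470 = 0.498.
- Pain, equal split: 2 × 0.774 × 0.226 = 0.350.
- No effect in either group: 2 × 0.05 × 0.95 = 0.095.

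| Assumed split | RMDQ powers | RMDQ: exactly one | Pain powers | Pain: exactly one |
|---|---|---|---|---|
| 50/50 | 53 %, 53 % | 50 % | 77 %, 77 % | 35 % |
| 40/60 | 44 %, 61 % | 51 % | 68 %, 85 % | 38 % |
| 30/70 | 34 %, 68 % | 56 % | 54 %, 90 % | 47 % |
| 20/80 | 24 %, 74 % | 63 % | 38 %, 93 % | 60 % |

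**Step 4. What an interaction contrast could detect.** With a and b completers per arm in the two groups, SE = SD × √(2/a + 2/b). Power (normal approximation) = Φ(difference/SE − 1.96). The difference detectable with 80 % power is (1.96 + 0.8416) × SE.
- Equal split: √(2/24 + 2/24) = 0.408.
 - Pain: SE = 2.5 × 0.408 = 1.02. For a 2.0-point difference between groups, 2.0/1.02 = 1.96, power 50 %. Detectable with 80 % power: 2.9 points.
 - RMDQ: SE = 5.0 × 0.408 = 2.04. For a 3.0-point difference, 3.0/2.04 = 1.47, power 31 %. Detectable with 80 % power: 5.7 points.
- 20/80 split: power 35 % (pain) and 22 % (RMDQ); detectable differences 3.6 and 7.2 points (7.15 before rounding).

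These are change-score approximations. The planned longitudinal model may be somewhat more precise, but that does not alter the comparison.

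**The case against.** The strongest case on the other side has four parts.

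1. **The age analyses are exploratory, and no comparison of p values is planned.** Both points are true. The primary methods also call for mean differences with standard errors and confidence intervals, not p values alone. A reader might infer that the results will be misread, but the document does not support that as a prediction. The figures above show how often a discordant pair would arise, not that anyone will misuse it.

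2. **Interaction terms are commonly left to the SAP, which is not shown.** This stands for subgroups where the article is merely silent. It does not cover age, where the article fixes both a purpose and a method and the two do not match.

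3. **The point does not extend to every subgroup.** A reader might infer that all the subset analyses are faulty and that no claim should rest on a within-subset test. The documents do not support this. The PTSS hypothesis is superiority within PCL-C ≥30, with its own 80 % power figure, and a within-subset test answers it. GAD-7, PSQI and NSI name only the symptomatic subset, so no pair of results is planned that could disagree. For PHQ-9 the text leaves open which outcome is compared, and the question may again be within-subset.

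4. **An interaction test here is weak.** This is correct and has to be disclosed. It does not favour separate subset tests, because an interaction estimate with a wide interval shows how little the data can say, and two separate p values hide it.

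**Conclusion.** The point holds for age. The article labels age a confounder in two places, gives a rationale that concerns effect modification, and plans an analysis that addresses neither. With the planned effect identical in both age groups, exactly one group would be significant about 50 % of the time for the RMDQ and 35 % for pain. This assumes an equal split, 24 completers per arm in each group, and the plan's own SDs and dropout. Over splits from 50/50 to 20/80 the ranges are 50–63 % and 35–60 %.

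The same reasoning reaches the PHQ-9 pair and high versus low PCL-C only if a difference between those subsets is to be claimed. The co-primary analyses and the PCL-C ≥30 hypothesis are unaffected. This is worth correcting in an exploratory analysis and does not threaten the trial's main conclusion.

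**What to change.** - In *Randomization* and in *Psychological and exploratory analyses*, describe age as a possible effect modifier and drop the confounding language.
- Estimate the treatment × age-group difference in the baseline-to-week-12 contrast from the full-sample longitudinal model already specified under *Primary outcome analyses*, and report it with its 95 % confidence interval.
- Show the estimates for the two age groups descriptively, and base any statement of differential response on the interaction estimate.
- Do the same for PHQ-9 and for high versus low PCL-C only if a difference between those subsets is to be claimed. Keep the pre-specified superiority test within PCL-C ≥30.
- State the limit: at an equal split, power is about 31 % for a 3.0-point RMDQ difference between age groups and 50 % for a 2.0-point pain difference, so a non-significant interaction does not show equal effects.

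The cost is a change of wording and one added model term with its contrast for each co-primary outcome. No new data or participants are needed.
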